**6. Statistical Analysis**

- All statistical analyses were performed using the principle of intention-to-treat analysis.
- For missing data, the data were analyzed by extrapolating the last observation.
- A two-way (time period and treatment group) repeated measures analysis of variance will be used to observe the difference in data between the two groups during the intervention period.

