**Treatment schedules**

**Duration and Frequency**

- Patients will be treated only as outpatients.
- Outpatient treatment shall be once a month for six months, with evaluation in the seventh month.
- In principle, the oral medication will be continued.

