**Change criteria: Combination therapy**

- If patient so wishes, a disclosure is given immediately, and Sham procedure can be changed to AKA-H method. A combination treatment is possible, with continuous administration of both the oral medicine and the analgesic patch.
- In the event that lower back pain ceases completely, and that patient does not wish to have treatment, this constitutes a complete recovery. In the event that patient wishes to terminate treatment or if deterioration of general condition of patients or the presence of an illness involving the vital prognosis is suspected, therapy is suspended immediately, and a thorough examination and appropriate treatment is performed.

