**5. Outcomes and Confidentiality**

Primary outcome and secondary outcomes

- Primary outcome is mean VAS score over a month from the previous visit.
- Participants are required to record their VAS score in a form every day at almost the same time for at least 1 month until the first visit and bring the recorded form along with consent form at the first visit.
- Secondary outcomes are Roland-Morris Disability Questionnaire (RDQ) and 36-Item Short-Form Health Survey (SF-36).
- Participants will fill RDQ and SF-36 at every visit including the first visit at the waiting room by advance reservation only before seeing a doctor. Participants are required to visit the outpatient office once a month, in principle, for 6 months after initiation of treatment.
- A VAS record form will be collected at every visit, and a new one will be provided to the participants.
- RDQ and SF−36 will be filled at the waiting room and will be collected at every visit. Those collected record forms will be stored in the locked locker at outpatient department.

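### Section 6 fixes last observation carried forward for missing data while patients may stop or leave sham on request, so the primary VAS comparison can be biased in either direction

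*Protocol*

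**What the plan says.** Protocol section 6 makes three statements that bear on this point:

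- Principle: "All statistical analyses were performed using the principle of intention-to-treat analysis".
- Missing data: "For missing data, the data were analyzed by extrapolating the last observation".
- Model: "A two-way (time period and treatment group) repeated measures analysis of variance will be used".

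Section 5 defines the endpoint: "Primary outcome is mean VAS score over a month from the previous visit". The VAS form is handed in and replaced at each visit, and RDQ and SF-36 are completed in the waiting room at each visit. The schedule in section 4 reads: "Outpatient treatment shall be once a month for six months, with evaluation in the seventh month".

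The part of section 4 on change criteria allows several departures from assigned treatment:

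- Recovery: "In the event that lower back pain ceases completely, and that patient does not wish to have treatment, this constitutes a complete recovery".
- The patient's wish: therapy is suspended "In the event that patient wishes to terminate treatment". It is also suspended if general deterioration or a life-threatening illness is suspected.
- Switching: "If patient so wishes, a disclosure is given immediately, and Sham procedure can be changed to AKA-H method". There is no corresponding route out of AKA-H.

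The protocol does not say whether diaries and questionnaires continue after a stop or switch, or whether values recorded after a switch are analysed or set to missing.

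**The concern.** Carrying the last value forward assumes that pain does not change after the last record, and it enters the filled months as if they had been measured. Both assumptions are doubtful over six months in patients whose pain may improve naturally. An arm that loses more patients, or loses them earlier, is held nearer its starting pain. The arms then differ for a reason unrelated to treatment.

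The protocol gives reason to expect that departures may depend on outcome and arm. Recovery is defined by pain itself. Patients enter by telephoning because they want AKA-H (section 4, Sampling and Recruitment), and only a sham patient has another procedure to move to after disclosure. Because forms change hands at visits, a patient who stops attending probably stops supplying data. The primary comparison is what is at stake.

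**Working it through.** **Inputs from the protocol.** Six monthly treatments with a closing evaluation, monthly mean VAS, carried-forward values for missing data, and repeated measures ANOVA. The protocol gives no sample size, SD, effect or dropout rate, so there is no figure to reproduce. Everything below rests on assumed inputs and illustrates the mechanism only.

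**Step 1: no true effect.** Assume a 0 to 100 mm VAS and a linear fall from B = 60 to E = 40 over six months in both arms. A fraction d of an arm is last observed at month m. The carried-forward arm mean at month 6 is

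(1 − d) × E + d × [B + (E − B) × m/6].

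The bracket is 56.67 for m = 1 and 50 for m = 3. Differences are AKA-H minus sham, so a negative value favours AKA-H.

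| Dropout AKA-H / sham | m | AKA-H mean | Sham mean | Difference |
|---|---|---|---|---|
| 10% / 30% | 3 | 0.9×40 + 0.1×50 = 41.0 | 0.7×40 + 0.3×50 = 43.0 | −2.0 |
| 10% / 30% | 1 | 0.9×40 + 0.1×56.67 = 41.67 | 0.7×40 + 0.3×56.67 = 45.0 | −3.3 |
| 30% / 10% | 3 | 43.0 | 41.0 | +2.0 |
| 30% / 10% | 1 | 45.0 | 41.67 | +3.3 |
| 20% / 20% | 1 or 3 | equal | equal | 0 |

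Timing matters as well. With 20% dropout in each arm, last seen at month 3 in AKA-H and month 1 in sham, the means are 0.8×40 + 0.2×50 = 42.0 and 0.8×40 + 0.2×56.67 = 43.33, a false difference of −1.3 mm.

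**Step 2: a true difference of −10 mm** (AKA-H to 40, sham to 50, same formula).

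- Equal 20% dropout gives −8.3 (m = 1) to −9.0 (m = 3), so the effect is diluted.
- 0% AKA-H / 30% sham gives −11.5 (m = 3) to −12.5 (m = 1), so it is exaggerated.
- 30% AKA-H / 10% sham gives −5.8 (m = 1) to −7.5 (m = 3), so it is strongly diluted.

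**Step 3: which route matters.** A simulation used 400,000 patients per arm, mean baseline 60 (SD 15), slope SD 2 mm per month and residual SD 8. It compared the carried-forward month-6 difference with the difference had everyone stayed on the assigned arm.

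- Recovery stops alone (VAS below 10, 80% chance of stopping each month): bias 0.00 to −0.01 mm. Only about 2% to 5% of patients stopped this way, and no separate recurrence process was modelled.
- Stops by patients at or above baseline, same rule in both arms: about 0 with no true effect, and +0.7 mm when the true difference was −9.8.
- Sham-only switching by patients at or above baseline (30% chance each month), last sham value carried forward: bias −3.6 to −4.6 mm, with 27% to 38% of sham patients switching.
- All routes together: −2.8 to −4.1 mm.

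In these scenarios the one-way switch drives the bias, provided that post-switch values are treated as missing.

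**Limit of the check.** These are month-6 contrasts. They do not give an error rate for the planned two-way ANOVA.

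**The case against.** The strongest reply is that stopping treatment is not the same as stopping data. Section 4 ends or changes treatment. It does not end diaries or visits, section 5 asks for monthly visits in principle, and section 6 states intention-to-treat. If patients keep recording, there is little to carry forward. A switched patient's later values would count under sham and would dilute a real effect, which works against AKA-H. This stands as a possible reading, but the protocol does not commit to it, and forms are collected and reissued only at visits.

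Second, patients are blinded and any of them may ask for disclosure. With no true effect, requests could be similar in both arms, and equal dropout with equal timing gave zero. This also stands: unequal dropout is an assumption, made plausible by the one-way switch but not shown.

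A reader might infer three stronger things that the documents do not support:

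- *The bias must favour AKA-H.* Step 1 gives either sign.
- *Recovered patients are frozen near zero and so favour AKA-H even without an effect.* With no effect, recoveries are alike in both arms, and recovery stops alone gave about zero. The carried value is a monthly mean, which may include painful days before recovery.
- *Lack of improvement is a listed reason to stop.* It is not. It can only be inferred from the freedom to stop or switch. The inclusion criterion on lack of improvement concerns earlier conservative care.

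Finally, sensitivity analyses may sit in an analysis plan that is not at hand, and their absence is not held against the protocol. That does not remove the point, because the protocol itself fixes the carried-forward rule.

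**Conclusion.** The point holds as a risk of bias in either direction, not as a demonstrated bias towards AKA-H. Two features combine: a missing-data rule that assumes no further change, and permitted departures that can depend on pain and on arm, with later data collection left unstated. On the assumed inputs with no true effect, a 20-percentage-point imbalance in dropout shifts the month-6 difference by 2.0 to 3.3 mm. Sham-only switching, with the last sham value carried forward, shifts it by 3.6 to 4.6 mm. The shift vanishes with equal dropout and timing under no effect. It does not arise through the switch if post-switch values are collected and kept. The actual size cannot be known from the protocol. The intention-to-treat statement does not settle the matter, because it does not make carried-forward values valid. The correction is cheap and should be made before the primary analysis is fixed.

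**What to change.** **Section 5.** State that VAS diaries, RDQ and SF-36 are collected through the seventh-month evaluation from all randomised patients, including those who recover, stop or switch.

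**Section 6.** Replace the carried-forward rule in the primary analysis with a likelihood-based mixed model for repeated measures, fitted to all observed monthly mean VAS values by randomised arm, without single imputation. State that values recorded after a switch are kept under the randomised arm. This follows intention-to-treat, and the text should acknowledge that it can dilute a real effect. Keep last observation carried forward only as a labelled sensitivity analysis.

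The mixed model is not assumption-free. It is valid when missingness depends on observed data such as recorded VAS, which is why continued collection comes first.

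**Cost.** One sentence in section 5, one paragraph in section 6, and a small extra follow-up effort for patients who stop treatment. The diary forms already exist. No clinical stopping or switching rule changes.

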**3. Study Design**

・Using a random number table created by free-software R (http://www.r-project.org), the patients were randomly assigned to the AKA-H (AKA-H) or the sham (S) groups.

・This study was a parallel group comparison in which the AKA-H group and S group were compared for 6 months. The study was randomized at the level of the individual patient, and it was a single-blind RCT in which only the patients were blinded to the details.

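### The repeated-measures ANOVA in section 6 leaves out the baseline values the trial already collects; it is valid but gives up precision that a baseline-adjusted model would recover

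*Protocol*

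**What the plan says.** Section 6 (Statistical Analysis) gives the model in one sentence: "A two-way (time period and treatment group) repeated measures analysis of variance will be used to observe the difference in data". The parenthesis lists the terms, and no covariate is among them. The window of the comparison is given as "between the two groups during the intervention period". The sentence does not say whether the pre-treatment month is one of the time levels, or whether the group effect or the time-by-group interaction answers the study question. The same section adds: "For missing data, the data were analyzed by extrapolating the last observation".

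Section 5 (Outcomes and Confidentiality) defines the outcome: "Primary outcome is mean VAS score over a month from the previous visit". It also secures a baseline, because participants must "record their VAS score in a form every day at almost the same time for at least 1 month until the first visit". RDQ and SF-36 are completed at each visit, starting with the first, before the patient sees the doctor.

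Under Duration and Frequency the schedule is: "Outpatient treatment shall be once a month for six months, with evaluation in the seventh month". That gives six post-treatment monthly means, or seven levels if the pre-treatment month is counted.

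**The concern.** Pain level before treatment usually predicts pain level afterwards. A model without baseline leaves that predictable variation between patients in the error term, so the interval for the group difference is wider and the power lower than they need be. The trial has already asked each patient for a month of daily recording, and that effort goes partly or wholly unused.

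Both readings of the sentence have a cost. If the pre-treatment month is outside the analysis, the baseline is ignored. If it is a time level, the group main effect averages in a month in which treatment cannot have acted.

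There is also a smaller, conditional matter. The classical univariate F-test for time-by-group relies on sphericity, and successive monthly pain means may well be more alike when close together in time than when far apart.

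**Working it through.** **Inputs.** From the protocol: two randomised arms, six post-treatment monthly means, one pre-treatment monthly mean, and a model with time and group only. The protocol states no alpha, power, effect, SD, correlation or sample size, so it has no figure to reproduce. The following are assumptions: 1:1 allocation, normal data, none missing, two-sided 5% level.

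**1. Baseline ignored versus adjusted.** Let r be the correlation of baseline VAS with the mean of the six post-treatment months. Then Var(adjusted) / Var(unadjusted) ≈ 1 - r². As an example, take an effect of 0.5 SD of that mean and 80% power, which needs 63 per arm unadjusted.

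| r (assumed) | 1 - r² | n per arm, adjusted |
|---|---|---|
| 0.3 | 0.91 | 63 × 0.91 = 57.3, so 58 |
| 0.5 | 0.75 | 63 × 0.75 = 47.3, so 48 |
| 0.7 | 0.51 | 63 × 0.51 = 32.1, so 33 |
| 0.8 | 0.36 | 63 × 0.36 = 22.7, so 23 |

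**2. Baseline as a seventh level.** With a constant effect δ after baseline, the group main effect estimates (0 + 6δ)/7 = 0.857δ. After rescaling to δ, the variance of the adjusted six-month comparison is 0.26 to 0.77 of the variance of this main effect. The structures tried were compound symmetry (0.3 to 0.7), AR(1) (0.5 to 0.9), and mixtures of the two. Against the contrast of post-treatment mean minus baseline, the ratio is 0.34 to 0.79.

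**3. The same contrast in power terms.** Assume 50 per arm, a monthly SD of 22 mm and a constant 10 mm effect. Let v be the variance of the contrast for a monthly SD of 1, so that SE = 22 × √(2v/50) and power ≈ Φ(effect/SE - 1.96). For the seven-level row the effect is 60/7 = 8.57 mm.

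| Analysis | AR(1) 0.8 | AR(1) 0.9 | Compound symmetry 0.5 |
|---|---|---|---|
| Six months, unadjusted: v | 0.680 | 0.824 | 0.583 |
| SE (mm); power | 3.63; 79% | 3.99; 71% | 3.36; 84% |
| Six months, adjusted: v | 0.438 | 0.330 | 0.333 |
| SE (mm); power | 2.91; 93% | 2.53; 98% | 2.54; 98% |
| Group effect over seven levels: v | 0.641 | 0.798 | 0.571 |
| SE (mm); power | 3.52; 68% | 3.93; 59% | 3.33; 73% |

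Simulation agrees: 71-83% unadjusted and 93-97% adjusted for the six-month contrast. The seven-level time-by-group test with Greenhouse-Geisser correction reached 46-75%.

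**4. Sphericity.** Simulated type I error at nominal 5%, with 8,000 runs per setting and 25 or 75 per arm:

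| Test | Compound symmetry | AR(1) 0.5 to 0.9 |
|---|---|---|
| Time-by-group, uncorrected, 6 levels | 0.050-0.051 | 0.066-0.091 |
| Time-by-group, uncorrected, 7 levels | 0.046-0.053 | 0.068-0.103 |
| Time-by-group, Greenhouse-Geisser | 0.038-0.049 | 0.042-0.057 |

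Under AR(1) the Greenhouse-Geisser epsilon runs from 0.77 down to 0.50 with six levels, and from 0.74 down to 0.44 with seven. The group main effect stayed at 0.044-0.054 in every setting, because it does not depend on sphericity.

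**The case against.** The strongest reply is that an unadjusted repeated-measures ANOVA in a randomised trial is a legitimate analysis, and that corrections and covariance structure commonly belong in an analysis plan, which is not at hand. For sphericity this stands. A reader might infer that the time-by-group p-value will be too small, but the protocol does not say that the interaction decides the question, nor that the F-test goes uncorrected. Under compound symmetry there is no inflation at all. For the covariate it does not stand: the protocol names its method and lists the terms, so this is a choice made, not a detail left open.

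A second reply is that if baseline is a time level, the interaction already uses it. That is fair, and it limits the claim. Assume 50 per arm, SD 22 mm, AR(1) 0.9 and an effect growing linearly to 12 mm. The corrected interaction test then has 72% power and the baseline-adjusted six-month mean 76%, a gap of a few points. A far larger gap appears if the seven-level group effect is set against an adjusted comparison at month 6 alone. Those are different contrasts, so that gap does not measure the value of adjustment. With a constant effect (10 mm, step 3) the adjusted comparison was clearly ahead of the corrected interaction.

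A reader might also infer that chance baseline imbalance biases the result. Under randomisation the unadjusted estimate is unbiased and its standard error already allows for such imbalance. This is the precision loss again and not a separate fault.

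**Conclusion.** The point holds as one of efficiency and should be fixed. The model named in section 6 is valid, but it does not adjust for a baseline that section 5 makes mandatory. Against an analysis that ignores baseline, adjustment cuts the variance by about 9% at r = 0.3, 25% at r = 0.5 and 49% at r = 0.7. Under the example in step 3 this lifts power for the same six-month contrast from 71-84% to 93-98%. The size of the gain in this trial cannot be read from the protocol, since r, SD, effect and sample size are all assumed here. The direction is firm, because the adjusted comparison had the smaller variance under every correlation structure tried.

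The inflation to roughly 7-10% is conditional on three things together: the time-by-group test being relied on, no correction being applied, and serial correlation of the AR(1) kind. The documents establish none of the three, and the group main effect is unaffected.

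**What to change.** Replace the model sentence in section 6 with a baseline-adjusted comparison of post-treatment monthly mean VAS. Either of two forms would do:

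- ANCOVA on the mean of the six post-treatment months, with arm and the pre-treatment monthly mean VAS as terms.
- A mixed model for repeated measures with arm, month, arm-by-month, baseline and baseline-by-month, and an unstructured covariance.

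State the contrast of interest, for example the arm difference averaged over the six months or at the last month. Use the same model for RDQ and SF-36 with their first-visit values. If a repeated-measures ANOVA is kept, say whether the pre-treatment month is a time level and apply a Greenhouse-Geisser correction to the time-by-group test. If the mixed model is chosen, bring the sentence on carrying the last observation forward into line with it, because that model can be fitted to the observed months without filling in values.

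The cost is a change of wording in section 6, submitted through the ethics review that section 9 requires for any change to the protocol. No extra data, visits or patient effort are needed.

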**7. Ethics**

**Protection of the Patients**

The study will be performed in accordance with the ethical principles in the Declaration of Helsinki.

**Informed consent for patients**

Prior to registration for the trial, the attending physician will provide patients with an informed consent form that meets the approval of the ethics committee of the Saitama Prefectural Rehabilitation Center, explain the tests sufficiently as dictated by the needs of the individual patient, and obtain the patients’ agreement in writing that they are participating in the trial of their own free will.

The informed consent form shall be signed or sealed and dated by the responsible research physician who provided the explanation. The physician in charge of the research shall provide patients with a copy of the signed or sealed and dated informed consent form with explanatory materials, and attach a copy of the form to their patient record prior to the patient's participation in the trial. The informed consent form shall be retained for one year.

Consent may be withdrawn at any time and may, as a general rule, be communicated by the patient himself or herself to the responsible physician during examinations or via phone call.

**Privacy Policy**

Identification and referral of registrants were performed through a randomly assigned registration number assigned at the time of registration. Personal data such as names, birth dates, addresses, phone numbers, et cetera are not shared or disclosed by the medical institution.

**Approval by Saitama Prefectural Rehabilitation Center Ethics Committee**

Prior to implementation of these trials and throughout the time scheduled for implementation of the trials, approval shall be obtained from the Saitama Prefectural Rehabilitation Center Ethics Committee for the implementation and continuation of the trials from the perspective of ethical, scientific, and medical propriety and validity. Research representatives shall submit to the Saitama Prefectural Rehabilitation Center Ethics Committee documents for its review, including trial implementation schedules, informed consent forms, etc.

**Changes to Protocol Contents**

In accordance with "9. Changes to Protocol Contents," when making changes to contents of the protocol, it will be necessary to submit an application for revision to the Ethics Review Board and to gain their approval.

**8. Expense Allocation & Compensation**

- Funding and Financial Relationships

There is no funding for the treatment, and there are no conflicts are interest (COIs).

- Expense Allocation for Testing

The clinical testing has no source of funding, so the subjects will be covered under their usual health insurance.

- Compensation for Health Damage and Insurance

Compensation for health damage shall be through the medical malpractice insurance of the physician in charge of research.

- Liability Insurance

The physician in charge of research shall have medical malpractice insurance. Subjects whose health has been damaged by researchers shall be receive in good faith the appropriate treatment as covered by health insurance.

**9. Changes to Protocol Contents**

In the event of changes to contents of the implementation planning document, it is necessary to submit a "written application for changes in protocol contents" to the Ethics Review Board of Saitama Prefectural Rehabilitation Center and to gain its approval beforehand.

In the event that the protocol is altered, physicians responsible for conducting the study will revise the explanatory documents given to subjects based on the changes.

